### Sample size calculation

2.4

According to a previous study on the effect of dried salted plum for HBOT induced otalgia,^[22]^ moderate to severe otalgia was present in 0.0% (0 of 53) of those consuming a dried salted plum vs 10.8% (4 of 37) of the control group (*P* = .026). Anticipating a power of 80% (1 – β = 0.8), statistical significance (α = 0.05) of 95%, and a dropout rate of 10%, a total of 76 participants for each group will be required in this study (https://clincalc.com/stats/samplesize.aspx).

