HBOT is a long-standing and well-established treatment for a wide variety of medical conditions, such as musculoskeletal injuries, infections, poor wound healing, hypoxia in neurons, carbon monoxide poisoning, decompression illness, and gas embolisms.^[2,4–7]^ Although HBOT is used in numerous pathological processes and is generally safe and well tolerated, certain effects and complications may occur during the treatment,^[8]^ some examples being middle ear barotrauma (MEB), claustrophobia, oxygen toxicity, myopia, pulmonary dyspnea, and oxygen-induced seizures.^[9]^ Among all the side effects of HBOT, MEB is a common one,^[10]^ with an incidence of approximately 2%.^[9]^ However, MEB is difficult to diagnose directly. Instead, it is mostly based on patients’ subjective reports of symptoms such as ear discomfort, stuffiness or fullness in the ear, and difficulties in equalizing ear pressure.^[11]^ Once a patient exhibits clinical signs and symptoms of MEB, s/he must be evaluated via otoscopic examination to diagnose and classify the extent of the injury. Only with proper grading of MEB can medical staff decide whether treatment is required or not. Treatments can take the form of enhanced equalization education, medical intervention, or surgical intervention such as myringotomy and ventilation tube placement. Currently, MEB is evaluated and graded with 3 methods: the Teed, Modified Teed, and O’Neill grading systems.^[12]^ It is hard to predict which patients may have difficulty equalizing middle ear pressure during actual hyperbaric exposure. In clinical practice, several methods are proposed to prevent MEB associated with HBOT. These include the Valsalva and Toynbee maneuvers to open the Eustachian tubes and facilitate pressure equalization,^[13]^ nasal decongestants to reduce hyperemia and edema of the middle ear mucosal lining,^[14]^ and prophylactic myringotomy or tympanostomy tube placement.^[15]^ To the best of the authors’ knowledge, no significant studies published to date have evaluated MEB prevention methods during clinical hyperbaric exposures.

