### Outcome measurements

2.6

The primary outcome measurement is the presentation of the tympanic membrane recorded according to the Modified Teed Classification, with grades from 0 to 5, where Grade 0 indicates symptoms with no ontological signs of trauma; Grade 1 indicates injection of the tympanic membrane; Grade 2 indicates Grade 1 plus injection plus mild hemorrhage within the tympanic membrane; Grade 3 indicates gross hemorrhage within the tympanic membrane; Grade 4 indicates free blood in the middle ear, evidenced by blueness and bulging; and Grade 5 indicates perforation of the tympanic membrane.

The secondary outcomes are symptoms of MEB and the overall ear discomfort levels. Recorded symptoms of MEB include feeling pressure in the ears, ear pain, headache, dizziness, vertigo, tinnitus, and hearing loss. The symptoms of MEB and the overall ear discomfort levels will be estimated using a 10-cm visual analogue scale with anchor points of 0 (no discomfort) and 10 (maximum discomfort) at the same time as the primary outcome measure. A higher score will indicate a higher level of discomfort during HBOT. The outcomes will be measured at baseline before the first HBOT, after the first 5 consecutive treatments of HBOT, and after each 10 treatments of HBOT until the twentieth HBOT.

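### The 80% power behind 76 per group was worked out for otalgia, a secondary symptom here, and is not shown to apply to the primary Modified Teed outcome

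*Protocol article*

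**What the plan says.** Section 2.4 of the protocol article starts from a single source: "According to a previous study on the effect of dried salted plum for HBOT induced otalgia". The rates taken from it are these: "moderate to severe otalgia was present in 0.0% (0 of 53) of those consuming a dried salted plum vs 10.8% (4 of 37") of the controls. The other inputs are "Anticipating a power of 80% (1 – β = 0.8"), "statistical significance (α = 0.05) of 95"% and "a dropout rate of 10"%. The section concludes that "a total of 76 participants for each group will be required in this study".

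Section 2.6 defines the primary outcome: "The primary outcome measurement is the presentation of the tympanic membrane recorded according to the Modified Teed Classification", on a scale from 0 to 5. It places ear pain among the recorded symptoms, which are secondary. Section 2.7 plans a chi-squared test for qualitative variables and a t test for quantitative ones.

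The only rate for middle ear barotrauma (MEB) is in the Introduction, which describes it as a common side effect "with an incidence of approximately 2"%. No Teed grade, unit (patient or session) or follow-up is attached to that figure.

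**The concern.** Section 2.4 is the article's only justification of trial size, so a reader will take its 80% as the power of the primary comparison. The inputs belong to something else: a pain symptom rather than an otoscopic grade, and a different preventive measure. Nothing in the article argues that otalgia rates carry over to the Teed scale. The assumed effect is also complete elimination, resting on 4 events against 0.

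What is at stake is how a non-significant Teed result will be read. With 80% power on record, it would be taken as reasonable evidence that self-acupressure does not prevent MEB. That reading needs a power figure for the Teed comparison, and the article contains none.

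**Working it through.** **Inputs.** Section 2.4: 10.8% vs 0%, α = 0.05, power 80%, dropout 10%, 76 per group. Sidedness is not stated; two-sided reproduces the stated number.

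**1. Reproducing the plan's figure.** Pooled normal formula for two proportions, with p̄ the mean of p₁ and p₂:

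n = [1.96·√(2p̄(1−p̄)) + 0.842·√(p₁(1−p₁) + p₂(1−p₂))]² / (p₁−p₂)²

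With p₁ = 0.108, p₂ = 0 and p̄ = 0.054:

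- 1.96 × 0.3196 = 0.626
- 0.842 × 0.3104 = 0.261
- (0.626 + 0.261)² / 0.108² = 67.6, so 68 evaluable per group
- 68 / 0.9 = 75.6, so 76

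The match is exact. The otalgia rates account for the whole calculation, and no Teed input is needed or used.

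**2. Sensitivity on otalgia itself.** The same formula solved for power is

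power = Φ{[|p₁−p₂|·√n − 1.96·√(2p̄(1−p̄))] / √(p₁(1−p₁) + p₂(1−p₂))}

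At n = 68 it gives 80% for 10.8% vs 0%, 47% for a 75% reduction (2.7%) and 21% for a halving (5.4%). The source rates are imprecise: the exact 95% intervals are 3.0% to 25.4% for 4/37 and 0% to 6.7% for 0/53.

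**3. What 68 evaluable per arm could detect on the primary.** The article states no Teed cut-off, distribution or effect. For illustration only, I assume a yes/no outcome of Teed grade 1 or higher, and I assume the control rates. Same formula, two-sided 0.05:

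| Control | Self-acupressure | Power |
|---|---|---|
| 20% | 4.4% | 80% |
| 30% | 10.8% | 80% |
| 40% | 18.3% | 80% |
| 20% | 10% | 37% |
| 30% | 15% | 55% |

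Example, 20% vs 10%: 0.10 × √68 = 0.825; 1.96 × √(2 × 0.15 × 0.85) = 0.990; √(0.16 + 0.09) = 0.5; Φ[(0.825 − 0.990)/0.5] = Φ(−0.33) = 37%.

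**4. If the Introduction's 2% were the per-patient control rate (unit not stated), with complete prevention.** By the formula: 0.02 × √68 = 0.165; 1.96 × √(2 × 0.01 × 0.99) = 0.276; √(0.02 × 0.98) = 0.14; Φ(−0.79) = 21%.

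The normal approximation is poor with so few events, so here is the exact figure for the uncorrected chi-squared test. With no events in the treated arm and a in the control arm, χ² = 136a/(136−a). Three events give 136 × 3/133 = 3.07, below the critical value 3.84; four give 136 × 4/132 = 4.12, above it. Power is therefore P(at least 4 of 68 at 2%) = 4.8%.

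**5. The two methods differ.** By the same exact test, 10.8% vs 0% has P(at least 4 of 68 at 10.8%) = 94% power, not 80%. The article's 80% is thus a normal-approximation figure, and the two kinds of figure should not be mixed in one statement.

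**The case against.** A reader might infer that the trial lacks 80% power for its primary outcome. The documents do not support that. Section 2.4 never ties its 80% to the Teed grade, and no Teed rate or effect is given against which to call the power short. The table above includes plausible-looking scenarios that reach 80%. An analysis using the full 0 to 5 scale, which section 2.7 does not rule out, would have a different power again.

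The 2% is a weak benchmark for the same claim. It is background on side effects, and the Introduction adds that MEB is mostly recognised from patients' own reports. Scheduled otoscopy up to the twentieth treatment could find more. If the 2% were per treatment and the treatments independent (both assumptions), the cumulative risk would be 1 − 0.98²⁰ = 33%, a level at which a large reduction is detectable with 68 per arm. The low power at 2% is therefore a conditional illustration, not a finding about this trial.

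Borrowing a related symptom from another prevention study is a common and openly disclosed choice, and the article says that no acupressure data on HBOT-related MEB exist. The different intervention is not in itself an error.

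It could also be said that an article condenses its full protocol. That does not answer the point: section 2.4 gives a complete calculation that reproduces to the participant, and that calculation is for another endpoint.

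These arguments remove any claim that power is below 80%. The absence of a link between the stated power and the primary outcome remains.

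**Conclusion.** The concern holds in this form: the 80% and the 76 per group describe moderate-to-severe otalgia at 10.8% vs 0%, and are not shown to apply to the Modified Teed outcome. Power for the primary cannot be determined from the document.

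Under the yes/no assumption and the plan's own formula, it is 80% only if rates fall from 20% to 4.4%, 30% to 10.8% or 40% to 18.3%, each a reduction of more than half. A halving from 20% or 30% has 37% or 55%. If 2% were the per-patient rate, even complete prevention would have about 21% by the formula and about 5% by the exact chi-squared test. The endpoint mismatch is certain from the text; the power figures depend on the assumed cut-off and control rates.

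**What to change.** Keep 152 participants and the primary outcome, and amend section 2.4 to:

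- state that the 80% applies to otalgia at 10.8% vs 0% under the normal approximation, and was not derived for the Modified Teed outcome;
- add the Teed differences detectable with 68 evaluable per arm, using one method throughout and labelling the grade 1 or higher dichotomy and the control rates as assumptions;
- say that a null Teed result will not be read as adequately powered evidence of no effect.

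The cost is a few sentences and no extra participants. The downside is that the power claim for the primary outcome becomes less favourable. Making ear pain or discomfort the primary so that it fits the calculation is not advised: the trial is registered and recruitment began in March 2020, so this would change the question rather than correct the statement.

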### Interventions

2.5

All participants will receive education from trained practitioners on the Valsalva and Toynbee maneuvers before the first HBOT. The participants in the experimental group will undergo additional education and training in self-acupressure therapy. The acupoints used will be TE17 (Yifeng), TE21 (Ermen), SI19 (Tinggong), and GB2 (Tinghui) (Fig. 2). All acupoints have been selected and localized according to the WHO Standardized Acupuncture Point Location guidelines.^[23]^ The education on self-acupressure therapy will be provided by the same trained practitioner, who has received sufficient training from a licensed TCM doctor in Taiwan. The self-acupressure therapy protocol is as follows: In a sitting position, the patient applies firm pressure (3–5 kg of pressure) with the fingertips in a circular motion at a speed of 2 circles per second for a duration of one minute per acupoint, with 1 to 2 seconds of rest after each 10 circles. The complete process lasts for about 5 minutes. A weighing scale is used for calibrating the correct amount of finger pressure necessary for the acupressure treatment. The participants in the control group will receive routine Valsalva and Toynbee maneuvers before the first HBOT, without additional education on self-acupressure.

**Figure 2 F2:**
[figure not shown]
Acupoints used in the self-acupressure therapy: TE17, TE21, SI19, and GB2.

### Outcome measurements

2.6

The primary outcome measurement is the presentation of the tympanic membrane recorded according to the Modified Teed Classification, with grades from 0 to 5, where Grade 0 indicates symptoms with no ontological signs of trauma; Grade 1 indicates injection of the tympanic membrane; Grade 2 indicates Grade 1 plus injection plus mild hemorrhage within the tympanic membrane; Grade 3 indicates gross hemorrhage within the tympanic membrane; Grade 4 indicates free blood in the middle ear, evidenced by blueness and bulging; and Grade 5 indicates perforation of the tympanic membrane.

The secondary outcomes are symptoms of MEB and the overall ear discomfort levels. Recorded symptoms of MEB include feeling pressure in the ears, ear pain, headache, dizziness, vertigo, tinnitus, and hearing loss. The symptoms of MEB and the overall ear discomfort levels will be estimated using a 10-cm visual analogue scale with anchor points of 0 (no discomfort) and 10 (maximum discomfort) at the same time as the primary outcome measure. A higher score will indicate a higher level of discomfort during HBOT. The outcomes will be measured at baseline before the first HBOT, after the first 5 consecutive treatments of HBOT, and after each 10 treatments of HBOT until the twentieth HBOT.

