#### Exclusion criteria

2.3.2

Subjects will be excluded if they meet any of the following criteria:

1.pregnancy;2.acute disorders of the ears or upper respiratory tract;3.evidence of neurologic dysfunction precluding them from making an informed decision;4.tracheostomy or endotracheal intubation;5.myringotomy, tympanoplasty, mastoidectomy, or tympanostomy tube placement.

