### Statistical analysis

2.7

Quantitative variables, presented as mean ± SD, will be analyzed by the Student *t* test. Qualitative variables, expressed as a number (percentage), will be analyzed using the Chi-Squared test. All analyses will be performed in SPSS software. Differences will be considered statistically significant at *P* < .05.

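### The secondary symptom scores can include complaints present before any HBOT, and the tests named do not adjust for the baseline scores that the trial collects

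*Protocol article*

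**What the plan says.** Section 2.6 of the protocol article sets the symptom outcome: "The secondary outcomes are symptoms of MEB and the overall ear discomfort levels". It then lists what is recorded: "Recorded symptoms of MEB include feeling pressure in the ears, ear pain, headache, dizziness, vertigo, tinnitus, and hearing loss". The symptoms and overall ear discomfort are scored on a 10-cm VAS, and "A higher score will indicate a higher level of discomfort during HBOT". On timing, "The outcomes will be measured at baseline before the first HBOT", then after the first five treatments and after each ten up to the twentieth.

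The primary outcome is separate and otoscopic: "The primary outcome measurement is the presentation of the tympanic membrane recorded according to the Modified Teed Classification, with grades from 0 to 5".

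Among the ear and airway conditions that bar entry (section 2.3.2) are "acute disorders of the ears or upper respiratory tract" and a list of ear procedures. Chronic tinnitus, hearing loss, headache or dizziness is not listed. The Introduction names, among the general uses of HBOT, "hypoxia in neurons, carbon monoxide poisoning, decompression illness, and gas embolisms".

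Section 2.7 assigns quantitative variables to the Student t test. For the rest, "Qualitative variables, expressed as a number (percentage), will be analyzed using the Chi-Squared test". It mentions neither a baseline covariate nor a change score. Section 2.2 says that the two groups are nonrandomized and recruited in different time periods.

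**The concern.** The trial asks whether self-acupressure prevents or reduces MEB associated with HBOT. A tinnitus or headache score recorded before the first session cannot come from HBOT, yet it sits under the same label and on the same scale as a score recorded afterwards. If post-treatment scores are compared by a plain t test, a long-standing complaint enters the comparison as if it were part of the outcome.

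Two things follow. Variation between participants in unrelated complaints widens the standard error and can hide a real benefit. And because the groups come from different calendar periods, the mix of treated illnesses may differ between them. A difference in background complaints would then pass straight into the treatment comparison, for or against self-acupressure. At stake is how far the secondary symptom results can be interpreted.

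**Working it through.** **1. The plan's own figure.** Section 2.4 uses 10.8% vs 0%, power 80%, alpha 0.05 and dropout 10%. With the pooled rate (0.108 + 0)/2 = 0.054, two-sided and without continuity correction:

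n = [1.96·√(2·0.054·0.946) + 0.8416·√(0.108·0.892)]² / 0.108² = (0.6265 + 0.2612)² / 0.011664 = 67.6, so 68 per group. Then 68/0.9 = 75.6, so 76.

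The stated 76 per group reproduces. It does not depend on the present point; I use it only for the 68 evaluable participants per group.

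**2. Can background complaints enter?** Side by side: section 2.6 lists five non-specific complaints as MEB symptoms; section 2.3.2 does not exclude patients who have them chronically; section 2.6 scores them before any HBOT; section 2.7 names two tests that, as named, do not adjust for baseline. So they can enter, unless an unshown document brings in the baseline.

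**3. Noise (illustration; every input except n = 68 is assumed).** Write a post-treatment VAS score as an MEB part with variance 1 plus a stable background with variance v. Let the true effect be 0.5 SD of the MEB part, and let the baseline score equal the background plus error with variance e = 0.1.

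- Unadjusted variance: 1 + v.
- ANCOVA residual variance: 1 + v − v²/(v + e).
- Power ≈ Φ(0.5/√(2·variance/68) − 1.96).

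For v = 1, unadjusted: variance 2, standard error √(4/68) = 0.2425, 0.5/0.2425 = 2.06, power Φ(0.10) = 0.54. ANCOVA: variance 2 − 1/1.1 = 1.091, standard error 0.1791, 0.5/0.1791 = 2.79, power Φ(0.83) = 0.80. With the t distribution instead of the normal these become 0.53 and 0.79.

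| v (assumed) | Unadjusted | ANCOVA |
|---|---|---|
| 0 | 0.83 | 0.83 |
| 0.25 | 0.74 | 0.80 |
| 0.5 | 0.66 | 0.80 |
| 1 | 0.54 | 0.80 |
| 2 | 0.39 | 0.80 |

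The recovery depends on a stable background. At v = 1, raising e to 0.5 gives residual variance 2 − 1/1.5 = 1.333 and power 0.71; e = 1 gives 1.5 and 0.66. Both still exceed 0.54.

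**4. Bias.** If mean background differs by Δ between the two recruitment periods, the unadjusted difference is the true effect plus Δ, and Δ can have either sign. ANCOVA with slope v/(v + e) leaves Δ·e/(v + e). With e = 0.1 that is 0.29Δ at v = 0.25 (0.1/0.35), 0.09Δ at v = 1 (0.1/1.1) and 0.05Δ at v = 2 (0.1/2.1). Adjustment thus removes most but not all of an imbalance that the baseline score captures, and none of what it does not capture.

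**The case against.** The best defence is that this is a condensed article. Baseline scores are collected, so pre-existing complaints can be separated; a change from baseline is itself a quantitative variable that a t test could compare; the VAS sentence refers to discomfort during HBOT; and attribution rules may stand in a fuller document. This stands in part. Silence about cause is no finding, and the article does not say that raw post-treatment values will be compared. But the article does fix the symptom list and name the tests, and those tests carry no baseline term although the scores exist and the arms are non-concurrent. The sentence about discomfort during HBOT cannot describe a score taken before the first session and sets no rule on onset.

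A reader might infer more than the text supports:

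- *That complaints count as MEB whatever their cause.* No sentence says so. MEB itself is graded by otoscopy, and these are secondary scores.
- *That steady tinnitus of 4 and new ear pain of 4 give the same outcome.* This needs a pooled or any-symptom score, which the article never defines.
- *That power can be worked out by adding a background rate to 10.8% vs 0%.* Those are rates of moderate to severe otalgia, not of any listed symptom; the VAS has no stated cut-off; and the 0% arm drives the result. With no background at all, a 2% rate in place of 0% already lowers exact chi-squared power at 68 per group from 94% to 59%.
- *That the effect is pure dilution.* This needs equal background in both arms, which different recruitment periods do not assure.
- *That ear pressure and ear pain should rank above the other symptoms.* That is a clinical choice, and the statistical point does not need it.

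**Conclusion.** The point holds in a limited form. The symptom outcome takes in non-specific complaints that eligible patients may bring with them, and the named tests leave unused the baseline that would separate them. The result is extra noise and, where case mix differs between periods, possible bias in either direction.

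The document supplies no prevalence, SD or baseline correlation, so no actual loss can be stated. The illustrated gain at v = 1 rests on the assumed 0.5 SD effect, a stable background and a small baseline error; it shrinks as the background fluctuates. The Introduction's list of HBOT uses is general background and does not establish this trial's case mix. The primary outcome and the sample size are untouched. This is a worthwhile, low-cost improvement to a secondary analysis, not a flaw in the main result.

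**What to change.** In sections 2.6 and 2.7, state that each symptom's VAS score, and overall ear discomfort, will be analysed separately at each post-baseline visit by ANCOVA, with group and the participant's own baseline score as terms, in place of an unadjusted t test. If symptoms are also reported as counts, count as new only those absent at that participant's baseline, and do not label baseline complaints as symptoms of MEB.

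The cost is wording. The baseline scores are already collected and SPSS fits the model, so no visit, measurement or participant is added. The downside is small: one more covariate per model, and participants who already have a symptom leave the new-onset count for that symptom. The adjustment does not turn non-concurrent arms into randomized ones, and the report should say so.

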### Statistical analysis

2.7

Quantitative variables, presented as mean ± SD, will be analyzed by the Student *t* test. Qualitative variables, expressed as a number (percentage), will be analyzed using the Chi-Squared test. All analyses will be performed in SPSS software. Differences will be considered statistically significant at *P* < .05.

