**Methods::**

This is a prospective nonrandomized controlled study. A sample of 152 participants will be assigned to 2 groups in a 1:1 ratio. The participants in the control group will receive conventional Valsalva and Toynbee maneuvers, while those in the experimental group will be given additional self-acupressure therapy. The acupoints used will be TE17 (Yifeng), TE21 (Ermen), SI19 (Tinggong), and GB2 (Tinghui). The Modified Teed Classification, symptoms of MEB, and overall ear discomfort levels will be assessed. Data will be analyzed using the Chi-Squared test or *t* test.

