### Study design

2.2

This prospective nonrandomized controlled trial began at the HBOT center at KCGMH in southern Taiwan in March 2020 and will continue through February 2022. The recruited participants will be assigned to the experimental group (conventional Valsalva and Toynbee maneuvers plus self-acupressure therapy, n = 76, expected) or the control group (conventional Valsalva and Toynbee maneuvers, n = 76, expected). All participants will receive education on the Valsalva and Toynbee maneuvers before the first HBOT. Participants in the experimental group will receive additional self-acupressure education from the same trained practitioner before the first HBOT. Because participants could learn the technique of self-acupressure from each other while receiving HBOT in the same chamber, the participants in the experimental and control groups will be recruited separately in different time periods. The study design has been written in accordance with the Consolidated Standards of Reporting Trials (CONSORT) 2010 guidelines.^[21]^ The overall schematic chart is provided in Figure 1.

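### Group is fixed by recruitment period without randomisation, yet the only stated comparisons are unadjusted t and chi-squared tests, which cannot separate an acupressure effect from a case-mix or period difference

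*Protocol article*

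**What the plan says.** The Abstract states the design: "This is a prospective nonrandomized controlled study". It also says "A sample of 152 participants will be assigned to 2 groups in a 1:1 ratio". Section 2.2 (Study design) explains what determines the group: "the participants in the experimental and control groups will be recruited separately in different time periods". The reason given is contamination: "Because participants could learn the technique of self-acupressure from each other while receiving HBOT in the same chamber". The Discussion repeats this. The study runs "in southern Taiwan in March 2020 and will continue through February 2022". The number, length and order of the recruitment periods are not given.

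Section 2.7 (Statistical analysis) states the comparison: "Quantitative variables, presented as mean ± SD, will be analyzed by the Student" t test, then a chi-squared test for qualitative variables, SPSS, and significance at P < .05. The Abstract names the same pair: "Data will be analyzed using the Chi-Squared test or" t test.

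Section 2.6 (Outcome measurements) says "The outcomes will be measured at baseline before the first HBOT", and then after 5 treatments and after each 10 up to the twentieth. Section 2.7 does not say how the baseline values enter the comparison. The Abstract, Introduction and Discussion frame the aim as efficacy.

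**The concern.** An unadjusted two-sample test answers a question about efficacy only if the groups are alike apart from treatment. Randomisation would support that assumption. Here the recruitment period decides the group, so whatever else differs between the periods goes into the estimated effect.

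There is room for such differences. Section 2.3.1 admits any adult prescribed a first course of HBOT, with no restriction by indication, and the Introduction lists indications from poor wound healing to carbon monoxide poisoning. Ear and nasal history, season, and staff or chamber practice could also differ over a two-year window.

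The primary comparison and the efficacy claim built on it are at stake. Such a bias could favour either group, and it would not shrink with a larger sample.

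**Working it through.** **Step 1. Reproduce the plan's sample size.** Inputs from section 2.4: 10.8% (4/37) vs 0.0% (0/53), power 80%, α = 0.05, dropout 10%. Two-sided α is assumed, because it reproduces the stated figure.

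With pooled variance and mean risk p̄ = (0.108 + 0)/2 = 0.054:

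n = [1.960·√(2·0.054·0.946) + 0.842·√(0.108·0.892)]² / 0.108² = (0.6265 + 0.2612)² / 0.01166 = 67.6, so 68 per group.

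68/0.9 = 75.6, so 76 per group, as stated. The number is not in dispute, but like the planned tests it assumes groups that differ only by treatment. The checks below use 68 evaluable per group.

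**Step 2. Chi-squared test with no acupressure effect.** The outcome is taken as a yes/no event (an assumption, since section 2.7 does not say how Teed grades are grouped). Every pair of event counts (x, y) from 0 to 68 is weighted by its two binomial probabilities. The weights are summed over pairs where the uncorrected Pearson statistic exceeds 3.84. The two risks differ only because the periods differ. The 10.8% comes from section 2.4 and the 2% from the incidence of middle ear barotrauma quoted in the Introduction; all other risks are assumptions.

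| Risk in one period | Risk in the other | Chance of P < .05 |
|---|---|---|
| 10.8% | 10.8% | 5.0% |
| 10.8% | 8% | 8.7% |
| 10.8% | 5% | 24.3% |
| 20% | 10% | 37.0% |
| 4% | 2% | 8.4% |
| 2% | 2% | 2.4% |
| 2% | 1% | 2.5% |

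At about 2% the test is conservative even without drift, so a drift to 1% does not lift the rate above the nominal 5%.

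**Step 3. t test with no acupressure effect.** For an assumed drift of d standard deviations, the noncentrality is d·√(68/2) = 5.831·d, with 134 degrees of freedom and critical value 1.978.

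| Drift d (SD, assumed) | Noncentrality | Chance of P < .05 |
|---|---|---|
| 0 | 0 | 5.0% |
| 0.1 | 0.583 | 8.9% |
| 0.25 | 1.458 | 30.4% |
| 0.4 | 2.332 | 63.9% |

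**Step 4. How many covariates can the data carry?** At the plan's own rates the expected number of events is 68 × 0.108 + 68 × 0 = 7.3, about 7, all in one group. That is too few for an ordinary logistic model with several covariates. With no events in one group, the ordinary odds ratio is not finite.

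**Step 5. What can adjustment remove?** If all controls come from one period and all acupressure participants from another, an indicator for period is the same variable as the indicator for group. No regression or weighting can then estimate both. Adjustment can remove only differences in factors that are measured and that overlap between the groups.

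**The case against.** The strongest points on the other side, and what stands of each:

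- **This is a short article, and a full plan may adjust.** Covariate lists and sensitivity analyses are commonly left to a fuller document. But the article states its tests twice, and an adjusted primary comparison would replace them rather than fill in detail.
- **Separate periods prevent contamination.** That is a legitimate reason, openly given. It does not remove the confounding that the choice creates.
- **The inflation may be small.** This stands. The documents give no estimate of drift. A reader might infer that the planned tests have a badly inflated error rate; the documents support only that they are unprotected against drift.
- **Adjustment will not cure the design.** This also stands. A reader might infer that a regression with a season term makes the comparison causal. It does not when group and period coincide, and season helps only where both groups were recruited in the same seasons.
- **Baseline values may add little.** This stands in part. Acute ear and upper respiratory disorders and previous ear procedures are exclusions, and everyone is starting a first course, so baseline Teed grades may vary little. The visual analogue scale rates discomfort during HBOT, which has no direct counterpart before the first session. A reader might infer that a sign already present at entry will be counted as an event, but section 2.7 does not say whether raw values or changes are tested.
- **Confidence intervals.** A reader might also infer that a planned interval is wrong. Section 2.7 plans none.

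**Conclusion.** The concern holds in this form: in a design where recruitment period sets the group, the stated unadjusted tests cannot distinguish an acupressure effect from a case-mix or period difference, and the baseline measurements have no stated use. This is a mismatch between stated analysis and stated design, and it affects the primary comparison.

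Neither the direction nor the size of any bias can be derived from the documents. Over the assumed drifts examined, the chance of a spurious P < .05 runs from no inflation (2.5%) to 37% for a binary outcome, and from 9% to 64% for the visual analogue scale. These figures rest on 68 evaluable per group, no true effect, a two-sided 5% test, a yes/no outcome for the chi-squared test and the assumed drift sizes. They show sensitivity to drift and do not predict it.

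**What to change.** In section 2.7, and correspondingly in the Abstract:

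1. Make the primary comparison adjusted. For the visual analogue scale, use ANCOVA on the baseline value. For Teed grade, use Firth-penalised ordinal or logistic regression, or a propensity score, because events may be few.
2. Prespecify a short list of measured factors: baseline value, age, sex, HBOT indication (in a few broad categories), and ear or nasal history where recorded.
3. Keep the t and chi-squared tests as unadjusted, supportive results.
4. State the number and order of the recruitment periods. State that adjustment handles measured case-mix only, and that group and calendar period are aliased if each group has one period.
5. Word the conclusion as an association with residual period confounding, not as proven efficacy.

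The cost is a little more analysis work, recording a few chart items (the article does not say that indication or ear history is captured), and a more cautious conclusion. Baseline outcomes are already collected.
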